#### Adverse events

All adverse events will be recorded. The study will be terminated prematurely for an individual participant when training is excessive and remains excessive after a reduction of the training intensity. Signs for overstrain are: excessive muscle pain during the training, prolonged post-exercise muscle pain, a severely uncomfortable feeling during or after the training and extreme (muscle) fatigue (OMNI scale > 6).

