The currently recommended voluntary exercises to maintain comfort and symmetry[6] are widely used in daily practice and assume that low-intensity training is beneficial and not harmful for boys with DMD. However, these recommendations are mainly based on theory and there is a need for more research to justify these recommendations and to define the optimal exercise programmes[26]. As we expect that a low-intensity training may slow-down the secondary decline of muscle endurance and functional abilities (figure 1), we developed the *No Use is Disuse *(NUD) study protocol to answer the clinically relevant questions whether low-intensity physical training in boys with DMD is beneficial and does not cause further harm. The NUD study is the first to examine the effects of low-intensity physical training in human subject with DMD and will fill part of the gap in current knowledge about the possible effects of training in boys with DMD. The study consists of two training intervention studies: study 1 "Dynamic leg and arm training for ambulant and recently wheelchair-dependent boys with DMD and, study 2 "Functional training with arm support for boys with DMD who have been confined to a wheelchair already for several years". This paper describes the hypothesis and methods of the NUD study.

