## Methods

### Study 1 Dynamic leg and arm training

#### Design

Study 1 is an explorative randomized controlled trial with multiple baseline measurements. Randomization is stratified according to the ambulatory status (ambulant/non-ambulant) of the boys and the boys are allocated to the intervention group or the control group in a 2:1 ratio. The intervention group receives dynamic exercise treatment, whereas the control group receives usual care (no specific intervention) during 24 weeks. After this period, the control group will also receive the physical training. Randomization is performed by an independent statistician. Despite randomization, differences in baseline characteristics between the intervention group and the control group may still be present due to the relatively small number of participants. For this reason, multiple baseline measurements are performed that will allow us to do within-subject analyses as well. Assessments are not blinded, because it was considered virtually impossible to prevent the boys from revealing their group allocation to the assessor.

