Boys are instructed to send their daily number of revolutions and their perceived levels of exertion to the primary investigator by a postal questionnaire once every two weeks, together with an overstrain questionnaire. Parents and their boys are informed by telephone when compliance is inadequate or when other problems (such as signs off overstrain: see adverse events) are identified and children are encouraged to resume the training or to adjust the training intensity.

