#### Adverse events

All adverse events will be recorded. The study will be terminated prematurely for an individual participant when training is excessive and remains excessive after a reduction of the training intensity. Signs for overstrain are: excessive muscle pain during the training, prolonged post-exercise muscle pain, a severely uncomfortable feeling during or after the training and extreme (muscle) fatigue (OMNI scale > 6).

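### Persisting overstrain ends the study, not only the training, for that boy; before T4 this can remove follow-up from the training arm alone and may favour training

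*Protocol article*

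**What the plan says.** The Adverse events section of Study 1 reads: "The study will be terminated prematurely for an individual participant when training is excessive and remains excessive after a reduction of the training intensity". Study 2 repeats the rule in its own Adverse events section. The triggers are signs felt in or after training: "Signs for overstrain are: excessive muscle pain during the training, prolonged post-exercise muscle pain, a severely uncomfortable feeling during or after the training", together with extreme fatigue on the OMNI scale. An earlier step exists. Under the Study 1 intervention, parents and boys are telephoned when problems appear and "children are encouraged to resume the training or to adjust the training intensity". Both Adverse events sections also state that every adverse event is recorded.

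Under Study 1, Design, "the control group receives usual care (no specific intervention) during 24 weeks", and then: "After this period, the control group will also receive the physical training". The randomised period ends at T4, 24 weeks after the baseline period. The planned groups are 20 training boys and 10 control boys. The Background asks whether the training "is beneficial and does not cause further harm".

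**The concern.** The sentence names both the study and the training, and it is the study that ends. Read literally, a boy who meets the rule has no further visits. No other part of the article says that he is still assessed or kept in the comparison.

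The trigger is excessive training, and control boys have none before T4. Loss under this rule during the randomised period can therefore come only from the training arm. It would consist of the boys who tolerate training least. Muscle endurance is a primary outcome that the article defines through peripheral fatigue, and extreme fatigue is one of the triggers. A link between being removed and doing worse is thus plausible, though not documented. If the link exists, the boys left in the training arm at T4 are a favourable subset.

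The harm question is touched too. The boys removed are those whose later course would show whether a decline persists or reverses. An analysis plan written later cannot recover visits that were never held.

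**Working it through.** **Inputs from the article.** 30 boys at 2:1, which gives 30 × 2/3 = 20 and 30 × 1/3 = 10, as stated under Sample size. Alpha is 0.05 (sidedness not stated; two-sided assumed). No effect size, SD or power is given, so there is no powered figure to reproduce.

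**Scale of the trial.** By the normal approximation, the difference detectable with 80% power is (1.96 + 0.84) × √(1/10 + 1/20) ≈ 1.09 SD. Power is about 25% for a true difference of 0.5 SD and 73% for 1.0 SD.

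**Simple bound.** Suppose a share p of the 20 training boys is lost and their mean T4 change would be 1 SD worse than that of the boys who stay. Then

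mean of all 20 = mean of stayers − p × 1 SD,

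so an analysis of stayers alone is too favourable by p SD: 1/20 = 0.05, 2/20 = 0.10, 4/20 = 0.20. The counts and the 1 SD are assumptions.

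**Simulation.** 100,000 trials per setting were run with a standard normal outcome, no true effect and 20 v 10 boys. A two-sample t-test stood in for the between-group contrast of the ANOVA. The k training boys with the worst overstrain score were removed; that score has correlation ρ with outcome. Both k and ρ are assumed. Cells show the bias towards training in SD, then the chance of a significant result in favour of training.

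| Boys lost (k) | ρ = 0 | ρ = 0.3 | ρ = 0.5 | ρ = 1.0 |
|---|---|---|---|---|
| 1 | 0.00; 2.5% | 0.03; 3.0% | 0.05; 3.5% | 0.10; 5.1% |
| 2 | 0.00; 2.5% | 0.06; 3.5% | 0.09; 4.6% | 0.18; 8.5% |
| 4 | 0.00; 2.5% | 0.10; 4.4% | 0.17; 6.4% | 0.33; 17.3% |

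The bias should be proportional to ρ. At ρ = 0.3 this predicts 0.3 × 0.099 = 0.030, 0.3 × 0.181 = 0.054 and 0.3 × 0.334 = 0.100, against simulated values of 0.029, 0.056 and 0.103.

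The chance of a significant result in the harm direction falls from 2.5% to 1.8-2.2% (one boy), 1.2-1.9% (two) and 0.5-1.5% (four) over ρ from 1.0 to 0.3. If all 20 boys are assessed and analysed as randomised, the bias is zero and the false-benefit rate is about 2.5%.

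**Which outcome this concerns.** Table 2 lists the Motor Function Measure at all visits, so the T4 argument applies to it. It lists the Six-Minute Bicycle Test at T0, T2 and T5. By the Study 1 visit schedule, T5 is four weeks after the end of training in one arm and 12 weeks into training in the other. That timing has to be reconciled separately, and the figures above should not be read as applying to the bicycle test at T4.

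**The case against.** The strongest reply is that the plan makes such losses unlikely. Intensity is set individually, rechecked at home within two weeks and lowered if there is pain or too much fatigue. Overstrain is screened every two weeks, and termination follows only if a reduction has failed. Nothing in the article supports a figure such as four boys out of 20. The triggers are signs of tolerance, and no text ties them to change in motor function; the Background even notes that work-induced damage can promote repair. A boy stopped after week 12 has already given his T3 data. The sentence may also be loose wording in a condensed article for stopping the training.

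Most of this stands, and it limits the claim to a conditional risk. It does not remove the point: the rule is stated rather than omitted, and a team following it to the letter would cancel the visits. If only the training was meant to stop, the same rewording is needed.

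Two stronger readings are tempting. A reader might infer that the T4 comparison is biased as it stands. The article gives no rate of removal and no relation to outcome, and with no relation the bias is zero. A reader might also infer that the harm signal disappears. It does not: the overstrain event is recorded as an adverse event, and each termination is visible. Only the later functional course and later adverse events would be lost.

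**Conclusion.** The point holds as a conditional risk. As worded, persisting overstrain ends the study for the boy, and before T4 this can happen only in the training arm of Study 1. If at least one boy meets the rule, is not assessed afterwards, and overstrain goes with worse outcome, the Motor Function Measure comparison may be tilted towards training. The shift would be about 0.03-0.10 SD for one boy, 0.06-0.18 SD for two and 0.10-0.33 SD for four, over assumed correlations of 0.3 to 1.0.

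These are modest beside a detectable difference of about 1.09 SD. The Discussion expects small training effects, and a reader might infer that the bias could equal the effect. The article puts no number on that expectation and calls the rate of decline unknown, so it supports no such comparison.

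Study 2 has one group. The argument about one-sided loss does not carry over; there the rule can only select the boys who contribute to the pre-post comparison.

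**What to change.** Leave the stopping criteria exactly as they are. In both Adverse events sections, reword the sentence so that meeting the criteria ends the training and not follow-up. State that the boy is invited to the remaining scheduled assessments, as far as he is willing and the investigator considers each test acceptable: through T4 and later in Study 1, and those remaining among T3-T5 in Study 2. State that in Study 1 he is analysed in the group to which he was randomised.

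The cost is a short edit in two places. The visits are already in the schedule and several take place at home. The real downside is the burden on boys who have stopped training because of overstrain, above all from the bicycle test, which asks for full effort with legs and then arms. That is why attendance and each test should remain optional for them.

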#### Sample size

The average rate of decline (mean and standard deviation (SD)) of muscle endurance and functional abilities in boys with DMD, as assessed with bicycle ergometry and the Motor Function Measure (MFM), is unknown. Therefore, no sample size can be calculated for these primary outcomes. However, it is anticipated that multiple baseline measurements will increase the chance of finding statistically significant changes in the selected outcome measures. For reasons of convenience, and because this RCT should be regarded as a first explorative study, we decided to include 20 boys in the intervention group and 10 boys in the control group.

#### Analysis

A two-way analysis of variance (ANOVA) will be used to examine the effects of dynamic leg and arm training on the primary outcomes. Secondary outcomes will be treated similarly or by non-parametric analyses dependent on the type of outcome (interval or ordinal). Data will be analyzed with SPSS version 16.0 and an alpha level of 0.05 will be used to decide on statistical significance.

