#### Study outcomes

Study outcomes include measurements at the levels of body functions and structures, activities and participation as defined by the International Classification of Functioning, Disability and Health (ICF) [29]. Environmental characteristics (school type and home status) are assessed at baseline. Demographic variables (age, weight and arm span), the use of medication (such as corticosteroids), any co-interventions and daily amount of physical activity are registered during each session.

The assessments of boys in the intervention group are conducted during the baseline period (T0: at baseline; T1: after 4 weeks; T2: after 8 weeks), the training period (T3: after 12 weeks; T4: after 24 weeks) and the follow-up (T5: 4 weeks after the end of the training; T6: 24 weeks after the end of the training). The assessments of boys in the control group are conducted during the baseline period (T0: at baseline; T1: after 4 weeks; T2: after 8 weeks), the control period (T3: after 12 weeks; T4: after 24 weeks), the subsequent training period (T5: after 12 weeks of training; T6: after 24 weeks of training) and during the follow-up (T7: 4 weeks after the end of the training). Assessments take place at the department of Rehabilitation of the Radboud University Nijmegen Medical Centre (T0, T2, T4, T6), but also at home (intervention group: T1, T3, T5; control group: T1, T3, T5, T7) to reduce the practical burden on the participants. All data are collected by the (trained) primary investigator (MJ). (figure 4)

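### Study 1's two-way ANOVA, on its natural reading, discards boys with missing visits, and overstrain stops can make that loss one-sided; a mixed model with continued assessment would be better

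*Protocol article*

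**What the plan says.** The Analysis section of Study 1 reads: "A two-way analysis of variance (ANOVA) will be used to examine the effects of dynamic leg and arm training on the primary outcomes". It adds "Data will be analyzed with SPSS version 16.0" and that "an alpha level of 0.05 will be used to decide on statistical significance". It does not name the factors, the visits entered or the SPSS procedure.

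Other sections show what the ANOVA has to handle:

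- **Size.** Under Sample size: "we decided to include 20 boys in the intervention group and 10 boys in the control group". No calculation supports this ("Therefore, no sample size can be calculated for these primary outcomes"); the section relies on the repeated baselines to improve the chance of significant results.
- **Visits.** Under Study outcomes, assessments in both arms are "conducted during the baseline period (T0: at baseline; T1: after 4 weeks; T2: after 8 weeks"), followed by T3 and T4 at 12 and 24 weeks of the training or control period. That makes five visits in the randomised comparison. Controls start training only after it.
- **Outcome schedule.** Table 2 lists the Motor Function Measure (MFM) at all visits, but the Six-Minute Bicycle Test at T0, T2 and T5 only.
- **Stopping.** Under Adverse events: "The study will be terminated prematurely for an individual participant when training is excessive and remains excessive after a reduction of the training intensity".

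**The concern.** Three places in the article point to a group-by-time ANOVA on repeated visits. Study 2, which has one group, uses a one-way ANOVA whose factor is named as time. Study 1 adds a control group, so its two-way counterpart is time by group. The Design section of Study 1 also says that the repeated baselines are there to permit within-subject analyses.

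The usual SPSS route for such an analysis, repeated-measures GLM, works on complete records: one missing visit removes the boy. This works against the plan's own reasoning. The extra visits are meant to add information, yet under this method each is a further chance to lose a boy.

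The stopping rule adds a second problem. Only a boy in training can meet it, so up to T4 it acts on the intervention arm alone, and on boys who tolerated training poorly. The Background asks whether training is beneficial and does no further harm. A comparison without those boys may lean towards yes on both counts.

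**Working it through.** **Inputs from the article.** 30 boys, 20 trained and 10 control, which agrees with the 2:1 ratio (30 × 2/3 = 20; 30 × 1/3 = 10). Five visits T0 to T4 for the MFM. There is no power, dropout or missed-visit figure to reproduce.

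**Assumed inputs.** The missed-visit rate m (1% to 10%, independent between visits), the number of trained boys who stop (1 to 4 of 20), and how much worse they are than boys who continue (0.5 to 1 SD).

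**Step 1: boys lost to complete-case deletion.** Expected loss = 30 × (1 − (1 − m)^v), where v is the number of visits entered. For m = 5% and v = 5: 30 × (1 − 0.95^5) = 30 × 0.226 = 6.8.

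| Missed per visit | 2 visits | 3 visits | 5 visits |
|---|---|---|---|
| 1% | 0.6 | 0.9 | 1.5 |
| 3% | 1.8 | 2.6 | 4.2 |
| 5% | 2.9 | 4.3 | 6.8 |
| 10% | 5.7 | 8.1 | 12.3 |

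Five visits fits the MFM. Three is the number listed for the bicycle test. Two would be, for example, T2 and T4 only. If boys leave for good rather than miss scattered visits, the loss is simply the number who leave: 3 at 10%, 6 at 20%.

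**Step 2: cost in precision.** Difference detectable with 80% power at two-sided 0.05, in SD units = (1.960 + 0.842) × √(1/n1 + 1/n2).

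- 20 v 10: 2.802 × √0.150 = 1.09 SD.
- 15 v 8 (about 77% of each arm, as at 5% over five visits): 2.802 × √0.1917 = 1.23 SD.

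**Step 3: bias from one-sided stops.** If k of 20 trained boys are left out and are d SD worse than those who continue, the completers' mean exceeds the arm's mean by (k/20) × d.

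- k = 1, d = 0.5: 0.025, about 0.03 SD.
- k = 3, d = 1: 0.15 SD.
- k = 4, d = 1: 0.20 SD.

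**Step 4: would a mixed model help?** Data were simulated 300 times with no true effect and between-boy SD 1. The trained boys with the worst observed change at T3 had their T4 removed.

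| Boys without T4 | Full data | Complete cases | Mixed model |
|---|---|---|---|
| 2 | 0.021 | 0.085 | 0.022 |
| 4 | −0.026 | 0.091 | −0.023 |

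Complete cases moved by 0.085 − 0.021 = 0.06 and by 0.091 + 0.026 = 0.12 towards training. The mixed model stayed within 0.004 of the full data. The set-up favours the mixed model, because stopping depended on a T3 value that was observed. Some fits gave convergence warnings. It illustrates the mechanism and does not forecast this trial.

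**The case against.** The strongest reply is that the Analysis section says neither repeated measures nor complete cases. A two-way ANOVA could use T2 and T4 only, or change scores, and would then lose only boys missing those visits. Which visits enter and how gaps are treated is detail that an article may leave to the full protocol or analysis plan. This stands in part: group by time is an inference, and the absence of missing-data rules is not the finding. But a method is named, and any version that compares the arms at T4 drops boys without T4, which is where the one-sided loss arises.

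A reader might infer that about 7 of 30 boys will be lost. The article does not support that. It rests on an assumed 5% per visit, independent, over five visits, and applies to the MFM only; three visits at 5% would lose about 4. Home visits at T1 and T3 are meant to lower the burden and may keep the rate low.

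A reader might also infer that the boys who stop are those in whom training did worst on the primary outcomes. The listed signs of overstrain are pain, discomfort and fatigue, not MFM or cycling decline, and stopping requires them to persist after intensity is reduced. The size of the bias is therefore assumed, and it is small beside a detectable difference of 1.09 SD in a trial that calls itself explorative. Adverse events are also recorded separately.

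Finally, a reader might infer that a mixed model by itself rescues these boys. It does not. Read literally, the rule ends the study for the boy, so later values do not exist for any model. Overstrain is screened every two weeks, so a stop can precede T3 and leave baseline data only. The model is unbiased only if missingness depends on observed data.

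**Conclusion.** The point holds as a poor match between the named method and the article's own visit schedule and individual stopping rule. On the natural group-by-time reading, run as repeated-measures GLM, the analysis discards boys with any missing entered visit: about 1.5 to 12 of 30 over five MFM visits if 1% to 10% are missed per visit, and fewer with fewer visits. On a change-score reading it still discards boys without T4.

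The direction of the overstrain loss follows from the design, because before T4 it can come only from the training arm. Its effect on the estimate, about 0.03 to 0.20 SD, depends entirely on assumed numbers of stops and assumed shortfalls. This is worth correcting because it bears on the no-harm question and the correction is cheap. It does not invalidate the trial.

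**What to change.** Replace the two-way ANOVA for the primary outcomes of Study 1 with a linear mixed model (the MIXED procedure in SPSS):

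- Use all available visits T0 to T4 of all randomised boys, in the arm allocated.
- Include arm, visit, arm by visit and ambulatory stratum.
- Make the arm difference in change from baseline to T4 the main contrast, and state how T0, T1 and T2 together define baseline.
- Enter the baseline visits as outcomes and not also as a covariate. That avoids using them twice and keeps in the model boys who stop before T3.

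Add one sentence saying that ending training for overstrain does not end outcome assessment, where the boy and his parents agree. This leaves the stopping rule untouched and supplies the T3 and T4 values that no model can recover. State that the analysis assumes missingness depends on observed data.

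For the bicycle test, Table 2 lists no T4, and its T5 falls after the randomised period. That row must be reconciled with the visit schedule before a T4 contrast can apply to it.

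The cost is slightly more modelling work and a few assessments of boys who have stopped training.

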### Study 2 Functional training with arm support

#### Design

Study 2 has an observational one-group design using repeated measurements, because we anticipate that it will not be possible to recruit a sufficient number of boys for an RCT in the Netherlands. This problem is related to the fact that boys with DMD who have been confined to a wheelchair already for several years often experience many barriers, such as a lack of time due to therapy obligations and homework. It is also virtually impossible for them to do without their electric wheelchair for a couple of days to build up the required arm support for this study. In addition, the number of boys at this stage in the course of DMD is low (i.e. an estimated 120 boys in the Netherlands) and, it is expected that some of these boys already use an arm support, which is an exclusion criteria for participation.

